#### Masking

The design of the study does not allow for masking the patient to the received treatment. However, this limitation is compensated by the objective measure of the main outcome variable (smoking abstinence) and the random allocation of patients into study arms. Additionally, researchers in charge of the statistical analysis will be blinded to the identity of patients in each treatment group.

## Interventions

The intervention strategy to follow in both arms is based on the five A’s of the clinical practice guideline by the Agency for Healthcare Research and Quality [4]: ask, advise, assess, assist, and arrange. This way, all patients will be questioned in person about their tobacco addiction, receive advice from their doctor or nurse to cease smoking, and their willingness to quit will be evaluated. Patients who accept the offered help for the month following consultation will be randomly assigned to the intervention or control group, where they will receive a personal intervention combining behavioral and pharmacological treatment based on scientific evidence [2–4]. The intervention will be organized into several follow-up sessions, either on-line via the chat-bot (in which case the patient can access the intervention at their convenience) or face-to-face with their healthcare professional in the healthcare center.

### Intervention group

Patients assigned to the intervention group will use a chat-bot whose script for the smoking cessation process has been developed using contents based on current evidence. Subjects will download a messaging application on their smartphone for this purpose and will access the chat-bot with an assigned personal password. The chat-bot will guide them through all the stages of the dishabituation process. The chat is bidirectional, employs multiple media formats, and provides patients with automatic, science-based advice on cognitive-behavioral, motivational, relapse-preventative, and problem-solving techniques. This will take place with different periodicity depending on the quit date and other characteristics of the patient (personal choice, type of tobacco use, personal risk situation, prescribed medication, abstinence-related symptoms, and the evolution of coping with abstinence). The chat-bot also offers information about useful medication to quit smoking prescribed by their healthcare professional, and will recommend how to face problems related to the cessation process through advice and relaxation exercises available in different formats, such as video, computer graphics, games, and web links. Additionally, the chat-bot incorporates gamification elements (games for adults for acquiring new knowledge and skills), including a system to earn scores and badges that will provide access to specific information depending on the abstinence period and the needs of the individual. Specific aspects of the game mechanics (score, levels for different abstinence periods) and dynamics (rewards, acknowledgment) will be developed. Contact with the patient will begin at day ^− 15^, where the above-mentioned strategies will be established, and daily interactive appointments will be set until the quit date. From this point, subjects will receive encouragement and acknowledgement messages that will be spaced out gradually until six months of abstinence. The patient can contact the chat-bot at any time, so the number and total time of interactions are a priori unknown and will be recorded as secondary variables. In terms of proactive contacts, the patient can choose their timing and frequency.

#### Control group

Patients assigned to the control group will receive the usual practice for smoking cessation, namely the different interventions by primary care nurses and physicians included in the services portfolio of the Madrid Regional Health Service (Service 415, Care for adult smokers) that consist of one or two visits prior to the quit date, follow-up visits after one week and one month, and subsequent control visits depending on whether the opportunity arises, the professional’s criteria, and the patient’s needs.

#### Variables

The collaborating healthcare professionals will deliver their data prior to the beginning of the study. The recruiting participants will record patient data and will be also responsible for their follow-up. All the information will be recorded on a form created for the trial (DCN). Each collaborator will access the form from their personal computer via the project’s website, using a code for personal identification. Two visits have been defined for data collection of patients: basal and at 6 months.

#### Main outcome variable

Continuous tobacco abstinence at 6 months (yes/no). In accordance to the recommendations by “the Russell Standard” [20], abstinence is confirmed when the patient declares to have smoked five or less cigarettes since the beginning of the abstinence period and after being validated with a co-oxymeter Pico+TM Smokerlyzer® that reads < 10 carbon monoxide particles per million (ppm) in exhaled air.

#### Secondary outcome variables

Quality of life of the patient measured via the EuroQol-5D-5 L, a generic questionnaire in their Spanish version validated for our setting [21] that comprises two parts. The first part consists of five questions on the health condition of subjects to explore five dimensions: mobility, self-care, usual activities, pain/discomfort, and anxiety/depression. Each dimension is measured on a 5-level scale. From these five questions, a single weighed score is obtained, the so-called utility index. The higher the score the better the health condition. To obtain this index, the algorithm proposed for Spain has been employed [22]. The second part consists of a visual analog scale (VAS) ranging from 0 (worst possible condition) to 100 (best possible health condition). The intergroup differences in the utility score at 6 months will be used to construct the quality-adjusted life years (QALYs) gained with the intervention.

#### Employed time

Number of consultations and total time (in minutes) will be recorded in the DCN by the healthcare professional and automatically registered from the chat-bot.

#### Cost-utility

Costs derived from the intervention will be calculated via a proxy of their cost-opportunity. The price of avoided visits, calculated from the average salary of the health worker’s professional category, will be categorized as “saved costs”. An uncertainty threshold will be estimated for all the applied costs comprising the time range attributable to each activity. The calculation of benefits will be done based on the QALYs, quantifying the total gain from the EuroQol-5D-5 L utilities in the intervention group at 6 months and assuming they will stay constant for one year.

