#### Secondary objectives

To assess the intervention effectiveness compared to usual practice as measured through self-reported continuous abstinence at 6 months.To assess the intervention effectiveness compared to usual practice in terms of the improvement in their quality of life measured by the EuroQol-5D-5 L questionnaire.To evaluate the cost-utility ratio of the intervention compared to usual practice in primary healthcare.To assess the intervention effectiveness in terms of improved adherence to pharmacological treatment for tobacco cessation.

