#### Main effectiveness analysis

Intergroup differences in the continuous abstinence rates at 6 months (main variable) will be analyzed with their CI 95%. Bivariate analysis: a Student’s t-test, or the Mann-Whitney U-test in case the hypothesis of data normality is rejected, will be used to compare the outcome between groups in the case of quantitative variables. For qualitative variables, either Pearson’s chi-squared test or Fisher’s exact test, when applicable, will be used. After adjusting for possible confounding factors, the odds ratio of the association will be calculated using a logistic regression model where the dependent variable will be the continuous abstinence (yes/no) and the independent variables will be patient-related variables and the study group. In all cases, statistical significance will be set at *p* < 0.05. Gained QALYs will be estimated at a population level with their relevant CI 95% via parametric analysis methods and bootstrap techniques. Cost-utility ratio: this aim is exploratory (there is no specific design for it). The cost-utility ratio will be calculated dividing the overall cost by the sum of potential gains expressed in QALYs. For normally distributed data, a multivariate sensitivity analysis will be conducted, making the costs fluctuate within the constructed range of uncertainty. For the same distribution, we will also make the benefits (QALYs) fluctuate within the CI 95%. In all cases, the analysis will be for intention-to-treat. The number of withdrawals, losses to follow-up, and subjects not complying with the protocol will be recorded together with the relevant reasons. Losses to follow-up will be considered as smokers in the analysis [24]. A participant will be considered lost to follow-up after missing two appointments, failing to be contacted by phone in at least two occasions, and having no registered explanation for it. Missing information on professionals and/or patients will be replaced using values from the baseline data.

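### The cost-utility benefit is defined in two conflicting ways: as a between-arm difference in one section, and as the intervention arm's total gain set against overall cost in others

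*Protocol article*

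**What the plan says.** Four places in the protocol article bear on this.

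- **Secondary objectives** sets a comparative aim: "To evaluate the cost-utility ratio of the intervention compared to usual practice in primary healthcare".
- **Secondary outcome variables** gives a between-arm benefit: "The intergroup differences in the utility score at 6 months will be used to construct the quality-adjusted life years (QALYs) gained with the intervention".
- **Cost-utility** gives a benefit with no control-arm term: "quantifying the total gain from the EuroQol-5D-5 L utilities in the intervention group at 6 months", with the utilities then held constant over one year. On the cost side, the same section has a partly comparative element: "The price of avoided visits, calculated from the average salary of the health worker’s professional category, will be categorized as “saved costs".
- **Main effectiveness analysis** gives the ratio: "The cost-utility ratio will be calculated dividing the overall cost by the sum of potential gains expressed in QALYs". It also says of cost-utility that "this aim is exploratory (there is no specific design for it".

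**The concern.** The objective asks what the chat-bot adds to usual practice and at what cost. That calls for a difference between arms in both costs and QALYs. The benefit in the Cost-utility section is the total for one arm, and the ratio in Main effectiveness analysis is built from totals.

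The distinction matters because controls are not untreated. The Interventions section gives both arms behavioural and pharmacological treatment, and Sample size expects 9.6% of controls to be abstinent at 6 months. Recruitment takes patients who attend a health centre for whatever reason, so some utility recovery unrelated to smoking could occur in both arms. Under the literal wording, all of this would count as benefit of the chat-bot. A chat-bot with no effect on utility could still be reported as producing QALYs.

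Two analysts working from this text could follow different sections and report different results.

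**Working it through.** **No plan figure to reproduce.** The document gives no utility, QALY, cost or ratio value. The check is therefore algebraic, with illustrative values marked as assumptions.

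**Inputs**
- n = 230 per arm (Sample size).
- T = 1 year, with the 6-month utility held constant (Cost-utility).
- gI, gC = mean utility gain per patient in the intervention and control arms (not given).
- CI, CC = mean cost per patient in the two arms (not given).

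**Step 1: the two benefit definitions**
- Cost-utility section, read literally: gI × T × n.
- Secondary outcome variables, scaled to the same n: (gI − gC) × T × n.
- Ratio of the first to the second: gI/(gI − gC). They agree only if gC = 0.

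**Step 2: illustration.** Assume gI = 0.02 and let gC run from 0 to 0.02. The literal definition always gives 0.02 × 1 × 230 = 4.60 QALYs.

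| Assumed gC | Literal (QALYs) | Between-arm (QALYs) | Overstatement |
|---|---|---|---|
| 0 | 4.60 | 4.60 | 1 |
| 0.005 | 4.60 | 3.45 | 1.33 |
| 0.010 | 4.60 | 2.30 | 2 |
| 0.015 | 4.60 | 1.15 | 4 |
| 0.020 | 4.60 | 0 | no limit |

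The factor does not depend on the time profile. If utility rises linearly to 6 months and then stays level to 12, the year's area is 0.75 × g. The literal benefit becomes 0.02 × 0.75 × 230 = 3.45 QALYs, and the between-arm benefit shrinks in the same proportion.

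The row with controls gaining half as much has one possible anchor in the plan. If utility gain came only from abstinence, the planning rates of 9.6% and 19.2% (double 9.6%) would give 0.192/(0.192 − 0.096) = 2. The document does not say that utility gain works this way.

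**Step 3: what this does to cost per QALY.** Write r = gC/gI and c = CC/CI. Suppose overall cost means the gross cost of the intervention arm. Then

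literal ratio ÷ incremental ratio = [CI/(gI·T)] ÷ [(CI − CC)/((gI − gC)·T)] = (1 − r)/(1 − c).

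With r = 0.5:
- c = 0 gives 0.5/1 = 0.5 (literal ratio too low);
- c = 0.5 gives 0.5/0.5 = 1 (the two errors cancel);
- c = 0.75 gives 0.5/0.25 = 2 (literal ratio too high).

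If usual care costs more than the chat-bot arm, CI − CC is negative and the comparison changes character. If overall cost is instead already fully net of usual-care costs, the numerator is incremental and the literal ratio is 1 − r = 0.5 of the incremental one. The text does not settle which applies, so the direction for cost per QALY cannot be stated.

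**Step 4: does the planned sensitivity analysis help?** It moves costs within their uncertainty range and QALYs within their confidence interval. Neither puts a control-arm term into a benefit defined without one.

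**The case against.** The strongest reply is that the sections can be read together. Only Secondary outcome variables says how QALYs are constructed, and it does so between arms. The Cost-utility section may simply total that gain over the treated group and extend it to a year. Visits can be avoided only relative to usual care, so the cost side already looks to the comparator, and overall cost may mean cost net of those savings. The aim is declared exploratory, the Discussion calls the quality-of-life assessment non-confirmatory and expects limited changes, and a journal article condenses its economic methods.

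Much of this stands. It rules out three stronger inferences that a reader might draw:

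- **That the plan is settled on an uncontrolled before-after analysis.** The Cost-utility section mentions no baseline, and Secondary outcome variables points the other way. This is one of two conflicting readings.
- **That cost per QALY is understated by half.** That needs a fixed numerator, and the numerator is itself in doubt.
- **That unequal arm sizes under simple randomisation distort the ratio.** If costs and QALYs are totals over the same arm, n largely cancels.

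The harmonised reading, though, has to be supplied by the reader. The Cost-utility section names the intervention group and no comparator, and the ratio is worded as a sum. Condensation excuses missing detail, but not two statements of the same quantity that disagree.

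**Conclusion.** The concern holds as an internal inconsistency. The benefit is a between-arm difference in Secondary outcome variables and an intervention-arm total in Cost-utility, and the ratio in Main effectiveness analysis is not worded as incremental. Followed literally, the latter two do not answer the comparative objective.

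The size is conditional. The factor of Step 1 follows from the two definitions alone; any number put on it, including the 2-fold example and the 4.60 QALYs, rests on assumed utility gains. The conclusion on overstatement applies to the QALY gain, not to the ratio.

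The consequence is limited to a secondary, exploratory aim. It should be corrected because the correction is cheap and the result could otherwise be read as incremental when it is not.

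**What to change.** State one definition in Cost-utility and Main effectiveness analysis, consistent with Secondary outcome variables:

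- **Benefit:** the between-arm difference in mean QALYs per randomised patient, in place of the intervention group's total gain.
- **Cost:** the between-arm difference in mean cost per randomised patient, in place of overall cost. Count avoided visits once: if each arm's visits are already costed, the difference contains the saving and it must not be deducted again.
- **Ratio:** the cost difference divided by the QALY difference.
- **Baseline utility:** say what part it plays. Secondary outcome variables uses the 6-month score, so any chance difference at entry carries through; adjustment for baseline utility is preferable.

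The change is one of wording and needs no new data. The between-arm definition already requires utilities in both arms, and Employed time provides for recording consultations and minutes. On timing, "Two visits have been defined for data collection of patients: basal and at 6 months"; baseline adjustment assumes that the EuroQol questionnaire is completed at the first of these as well as the second, which the text should confirm.

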#### Design

The clinical trial will be pragmatic, randomized, controlled, and multicentric. It will last one year, six months for recruiting and six months of follow-up. A cost-utility study will be conducted from the perspective of the funder for a 1-year timeframe. (Figs. 1,2)

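### Holding the 6-month utility gain constant for a year, as most naturally read, overstates one-year QALYs by about a third under a linear build-up, and no stated sensitivity analysis tests it

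*Protocol article*

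**What the plan says.** The Design section sets the horizon: "A cost-utility study will be conducted from the perspective of the funder for a 1-year timeframe". The same section describes the trial: "It will last one year, six months for recruiting and six months of follow-up". Under Variables, data collection is limited: "Two visits have been defined for data collection of patients: basal and at 6 months".

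Two places say how the benefit is built. Secondary outcome variables states: "The intergroup differences in the utility score at 6 months will be used to construct the quality-adjusted life years (QALYs) gained with the intervention". The Cost-utility section describes it as "quantifying the total gain from the EuroQol-5D-5 L utilities in the intervention group at 6 months" and continues "assuming they will stay constant for one year".

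On costs, the Cost-utility section says "Costs derived from the intervention will be calculated via a proxy of their cost-opportunity". It counts avoided visits as savings and names no period. The Main effectiveness analysis section divides overall cost by summed QALY gains. It varies costs within their uncertainty range and QALYs within their 95% confidence interval, and it labels the aim exploratory.

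**The concern.** A QALY gain is the area under the between-arm utility difference over time. Multiplying the month-6 difference by a full year treats that difference as present from the first day and still present on the last. Neither half of the year supports this.

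- **First half.** Allocation follows baseline data collection (Recruitment section), so the expected difference at baseline is zero. Under the inclusion criteria, patients accept help to quit in the following month, and chat-bot contact begins at day −15. Some build-up time is unavoidable.
- **Second half.** Nothing is measured after month 6, and no allowance is made for relapse.

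The QALY gain is the denominator of the cost-utility ratio, so an inflated multiplier passes straight into that result. The two descriptions of the gain also differ: one is a between-arm difference, the other a gain in the intervention group, which taken literally does not subtract the control arm.

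**Working it through.** The protocol gives no utility, QALY or cost figure, so there is no number of its own to reproduce. The check is in units of D.

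**Inputs**
- D: between-arm utility difference at month 6 (Secondary outcome variables). No value is given and none is needed.
- Difference at baseline: 0 in expectation, from randomisation.
- Horizon: 1 year (Design).
- Utility measured at months 0 and 6 only (Variables). The path between and after these points is therefore an assumption.

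**Plan as most naturally read:** D × 1 year = 1.00D.

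**What the trial observes.** Joining the two measurements in each arm gives a 6-month area of 0.5 × (u0 + u6)/2. The between-arm difference is 0.5 × (0 + D)/2 = 0.25D.

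**Adding months 6 to 12 at a constant D:** 0.5 × D = 0.50D. The total is 0.25D + 0.50D = 0.75D.

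**Overstatement** = 1.00/0.75 − 1 = 33.3%.

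**Other paths.** For a linear rise to full effect at month m and a plateau to month 12, the area is (1 − m/24)D. For a linear rise to month 6 and then a linear change to a fraction f of D at month 12, it is 0.25D + 0.5 × (1 + f)/2 × D.

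| Assumed path | One-year area | Excess of 1.00D |
|---|---|---|
| Full at month 1, then flat | 1 − 1/24 = 0.958D | 4.3% |
| Full at month 3, then flat | 1 − 3/24 = 0.875D | 14.3% |
| Linear to month 6, then flat | 0.75D | 33.3% |
| Linear to month 6, half left at month 12 | 0.25 + 0.375 = 0.625D | 60% |
| Linear to month 6, none left at month 12 | 0.25 + 0.25 = 0.50D | 100% |
| Linear rise continuing to 2D at month 12 | 0.25 + 0.75 = 1.00D | 0% |

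**Share beyond follow-up.** Months 6 to 12 supply 0.50/1.00 = 50% of the flat one-year gain and 0.50/0.75 = 67% of the build-up-and-plateau version.

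**Does the sensitivity analysis cover this?** Write the QALY gain as k × D. Varying QALYs within their 95% confidence interval moves D for sampling error. It leaves k at 1.00 in every run, although the table puts k between 0.50 and 1.00. The time path and duration are untested.

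**The case against.** The strongest reply is textual. The sentence does not say that crediting starts at day 0. To stay constant could mean only that the month-6 value is carried forward to month 12. With a linear rise before month 6, the plan would then already give 0.75D and nothing would be overstated. This reading is possible. It is the less natural one: it means constancy for six months rather than a year, and neither section mentions interpolating from baseline. Starting the year at month 6 would run to month 18, outside the one-year frame. An ambiguity worth a third of the result needs settling in any case.

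A reader might infer more than the text supports in three ways.

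- **That the overstatement is at least one third.** One third belongs to one assumed path. Earlier onset gives about 4% to 14%, and a difference still growing to month 12 can give none.
- **That benefits are extended past month 6 but costs are not.** The one-year frame is set for the whole cost-utility study, and the text is silent on the cost period. A mismatch would affect the ratio, not the QALYs. Its direction is also open, because avoided visits count as savings and later control visits are left open-ended.
- **That chat-bot support stops at month 6.** The plan says "subjects will receive encouragement and acknowledgement messages that will be spaced out gradually until six months of abstinence". That is counted from quitting, and patients may contact the chat-bot at any time.

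It is also fair to say that the constancy assumption is openly declared, that the aim is exploratory, and that the Discussion calls the quality-of-life assessment non-confirmatory and expects limited changes. This lowers the stakes. It does not make a full-year multiplier consistent with a baseline difference expected to be zero.

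**Conclusion.** The concern holds in a limited form. As most naturally read, the rule gives 1.00D where a linear build-up and plateau gives 0.75D, an excess of about one third. That figure rests on three assumptions: crediting from day 0, zero expected difference at baseline, and a linear rise to month 6. Other paths in the table give anything from 0% to 100%. The percentages apply to D whatever its sign, so a negative difference would be magnified in the same way.

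Three statements do not depend on the path: months 6 to 12 are extrapolated, the stated sensitivity analysis does not test that extrapolation, and no cost rule is written for those months. The point deserves correction because cost-utility is a named secondary objective, but it does not touch the primary abstinence analysis.

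**What to change.** 1. Compute QALYs in each arm as the area under the line from baseline to 6-month utility, and take the between-arm difference. Reword the Cost-utility section to match Secondary outcome variables, so that the gain is between arms and not within the intervention group.
2. If the one-year horizon is kept, add months 6 to 12 as a separate, labelled extrapolation, with scenarios from gain fully kept (0.75D in total under the linear rise) to fully lost.
3. State the cost assumption for the same months in both arms, so that both parts of the ratio cover the same period.
4. Report the 6-month within-trial result beside the one-year figure. Replacing the declared one-year horizon altogether is a matter of choice and is not required.

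The cost is revised wording and a few lines of analysis. Both utilities are already collected, so no new data are needed. The price is a smaller headline QALY gain.
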